Outcome 7	Smoking cessation	Measured by the following questions 1. Smoking status will be assessed by asking, “Do you currently smoke cigarettes” (yes/no)? 2. Motivation to quit will be assessed using the motivation to stop smoking (MTSS) scale [37]. Participants will be asked to classify themselves into one of the following six stages: (a) I do not want to quit smoking, (b) I think I should stop smoking but do not really want to, (c) I want to stop smoking but have not thought about when, (d) I REALLY want to stop smoking and intend to in the next 3 months; (e) I want to stop smoking and hope to soon, (f) I REALLY want to stop smoking and I hope to in the next month 3. Nicotine dependence will be assessed using the Fagerström test [38]—a questionnaire made up of 7 questions, the first scored as 0 and 1 (yes/no), and the remaining 6 multiple-choice questions scored from 0 to 3. The total test score ranges from 0 to 10, with higher scores indicating more intense physical dependence on nicotine 4. Cessation methods will be assessed by asking: Which of the following methods have you tried in the last 6 months (check all that apply): (a) nicotine replacement therapy, (b) cold turkey, (c) Champix®, (d) bupropion (Wellbutrin or Zyban), and or (e) behavioral support (e.g., smokers help line, cessation support group, cessation website, smartphone app)	Improved lifestyle behaviors	While smoking cessation is recommended for all current smokers with COPD, very few are offered such an intervention. Studies have suggested that even a brief intervention can be effective on reducing exacerbation rates [39]

*ACCEPT* Acute COPD Exacerbation Prevention Tool, *BMQ* Beliefs about Medicines Questionnaire, *CAT* COPD Assessment Test, *COPD* Chronic obstructive pulmonary disease, *EQ5D* EuroQoL 5-dimension, *MTTS* Motivation to Stop Smoking scale

We chose “prescription appropriateness” as the primary endpoint because it is the process of care outcome that is most directly affected by the intervention, and it has been frequently used in trials on computerized decision support tools [33]. Prescription appropriateness will be assessed by determining the concordance between the pulmonologist- and CTS-based treatment recommendations.

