Secondary clinical outcomes include medication adherence (outcome 2) and rate of moderate or severe exacerbations (outcome 3). Data for the clinical outcomes will be gathered through questionnaires and chart reviews, as well as by linking patient data to BC’s administrative health databases using a unique personal health number; these databases comprehensively capture all healthcare encounters of all legal residents in BC at an individual level, independent of payer [40]. Medication adherence will be assessed using the medication possession ratio. For outcome 3, we will apply a validated definition of moderate and severe exacerbations; moderate exacerbations will be defined as any outpatient physician visit for COPD followed by filling prescriptions for antibiotic or oral corticosteroids, and severe exacerbations will be defined as any hospital admission with the main discharge code of COPD [41].

For patient-reported outcomes, we will assess self-reported medication adherence, quality of life, and smoking cessation using follow-up questionnaire data. Self-reported medication adherence will be assessed using a specific version of Beliefs about Medicines Questionnaire (BMQ COPD), which has been shown to have excellent construct validity and to be a strong predictor of adherence behavior [42]. For determining the impact of the intervention on the patients’ health status and quality of life, we will administer two questionnaires: (1) the COPD Assessment Test (CAT) and (2) the EuroQoL 5-dimension (EQ5D). The CAT assesses the impact of COPD symptoms on a person’s daily activities [34], and the EQ5D is a validated tool used to measure a patient’s overall quality of life [36]. Smoking cessation will be assessed by determining patients’ smoking status, motivation to quit [37], physical nicotine dependence [38], and methods used to quit in the last 6 months.

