##### Data collection

The total duration of the trial is 30 months. Initially, all participating pulmonologists will be in the comparison arm. After 6 months, two randomly selected pulmonologists will be reassigned to the intervention arm every other month (Fig. 2). In month 18, the last two pulmonologists will be assigned to the intervention arm, and patient recruitment will continue until month 24. Follow-up data will be collected until month 30 to ensure 6 months of follow-up data for all patients.

To assess the primary endpoint, the prescribed versus recommended treatments will be automatically documented and collected in aggregate form under a unique identification (ID) code assigned to each pulmonologist. If a patient consents to the longitudinal component, a baseline study visit will be conducted that includes administration of questionnaires to collect clinical and patient-reported data to assess secondary outcomes (Fig. 4). Subsequently, two follow-up appointments will be arranged at 3- and 6-month post initial visit via telephone. If a patient sees an enrolled pulmonologist multiple times throughout the 24-month study period, the first visit with the pulmonologist will be used to mark the start of the follow-up period for longitudinal data collection, unless the pulmonologist was reassigned to the intervention arm between visits. In this case, if the patient has consented to the longitudinal component, the follow-up period will be reset during the first visit the pulmonologist is in the intervention arm, and the patient will be followed for another 6 months after the initial intervention arm visit.

To deliver the intervention package, site coordinators will set up automatic software triggers for all eligible patients seeing a pulmonologist allocated to the intervention arm. A trigger will launch when the pulmonologist opens a patient’s EHR chart during the patient encounter, and the ADI will be pre-populated with predictor values. If a predictor value is not retrieved from a patient’s EHR, the empty fields will be highlighted and will be fillable through dictation or by typing directly into the ADI computer interface. At the end of the encounter, the pulmonologist will print the customized patient tool that will be distributed by the research coordinator.

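### The six-month look-back of the quit-methods item does not fit the 3-month call: if asked then, half its window precedes the index visit and weakens that one contrast

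*Protocol article*

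**What the plan says.** In the protocol article, Table 1 (Study outcomes, outcome 7, item 4) fixes the wording of the cessation-methods question: "Which of the following methods have you tried in the last 6 months (check all that apply". The text below the table repeats the window, listing "methods used to quit in the last 6 months" among the smoking measures, so it is not a slip in the table.

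The same section takes patient-reported outcomes, including "quality of life, and smoking cessation using follow-up questionnaire data". Data collection sets the contacts: "two follow-up appointments will be arranged at 3- and 6-month post initial visit via telephone". There is also a baseline visit with questionnaires, whose content is not itemised.

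Follow-up starts at the patient's first visit with the pulmonologist. If that pulmonologist has since crossed over, "the follow-up period will be reset during the first visit the pulmonologist is in the intervention arm", and a further six months of follow-up begins.

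The text shown does not assign individual items to calls, and the participant flow chart (Fig. 4) is not reproduced.

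**The concern.** A look-back period should not reach past the start of the exposure it is meant to reflect. A six-month recall asked three months after the index visit covers three months before that visit and three months after it. A quit attempt made before the patient met the tool would then enter the data as a follow-up result.

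The question is a tick-list without dates, so a month-3 answer cannot be split by itself into before and after. A baseline answer, if item 4 is asked there, helps only in part. A patient who ticked nothing at baseline can be dated, because any month-3 tick must fall after the visit. For a patient who ticked a method at baseline, a month-3 tick for the same method remains ambiguous. The analysis plan therefore cannot fully restore what the question did not collect.

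At stake is the month-3 comparison of quit methods between arms. Background use before the visit is added to both arms and shrinks the difference.

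**Working it through.** The article gives no rate, effect size or power for the smoking outcome, so there is no figure of the plan's own to reproduce.

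**Step 1. Window arithmetic (documents only).** Inputs: recall of 6 months (Table 1, item 4); calls at 3 and 6 months (Data collection). Months before the index visit = max(0, 6 − t) for a contact at month t.

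| Contact | Window (months from index visit) | Pre-index months | Share |
|---|---|---|---|
| Baseline, t = 0 | −6 to 0 | 6 | 6/6 = 100% |
| Call, t = 3 | −3 to +3 | 3 | 3/6 = 50% |
| Call, t = 6 | 0 to 6 | 0 | 0/6 = 0% |

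Only the 3-month call has a mismatch. At baseline a wholly pre-index window is what is wanted.

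**Step 2. Reset patients (constructed example).** Take a comparison-arm visit at month 0 and a reset visit at month 4. The 3-month call after the reset falls at month 4 + 3 = 7 and looks back to month 7 − 6 = 1. Months 1 to 4 precede the reset visit. An attempt in months 1 to 3 would be reported at the comparison-arm 3-month call and could be reported again as an intervention-arm answer. The article does not say how often such gaps will occur.

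**Step 3. Size of the dilution (assumed rates).** Let q0 be the chance of trying a method in three months under usual care, and q1 the chance in the three months after the visit in the intervention arm. Assume that the pre-visit rate is q0 in both arms and that the two three-month periods are independent.

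- Comparison arm, six-month recall at month 3: 1 − (1 − q0)²
- Intervention arm: 1 − (1 − q0)(1 − q1)
- Difference: (1 − q0)(q1 − q0)

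The difference therefore keeps the fraction (1 − q0) of its true size q1 − q0.

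| q0 | q1 | True difference | Difference with six-month recall | Kept |
|---|---|---|---|---|
| 0.05 | 0.10 | 0.050 | 0.0475 | 95% |
| 0.10 | 0.20 | 0.100 | 0.090 | 90% |
| 0.20 | 0.30 | 0.100 | 0.080 | 80% |
| 0.30 | 0.40 | 0.100 | 0.070 | 70% |
| 0.40 | 0.50 | 0.100 | 0.060 | 60% |

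For the middle row, the month-3 answers would show 1 − 0.8 × 0.7 = 0.44 against 1 − 0.8 × 0.8 = 0.36, a ratio of 1.22. The post-visit rates of 0.30 and 0.20 have a ratio of 1.50. Method use that persists from before the visit would change these values.

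**Step 4. After the change.** With recall limited to the time since the index visit, the pre-index share at month 3 falls from 50% to 0%. At month 6 it is already 0%.

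**The case against.** The strongest objection is that the premise is inferred. No sentence says that item 4 is asked at month 3, and which call carries which item is commonly left to the full protocol or the case report forms. This stands as a limit on certainty, and the conclusion is conditional for that reason. It does not dispose of the point. The article fixes the recall wording and both contact times, draws smoking data from follow-up questionnaires in general, and makes no exception for this item.

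A second objection is that the recall period fits the design, since follow-up lasts six months and so does the look-back. That is right for the 6-month call, which needs no change. The two follow-up windows share months 0 to 3, but nothing in the article says the answers are to be read as separate intervals, so the overlap contradicts nothing in the plan.

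A third is that the item is one of four. This also stands. Current smoking, motivation to stop and nicotine dependence carry no six-month look-back.

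A reader might infer from the reset rule that comparison-phase attempts credited to the intervention would favour the tool. The documents do not support that. Months before the index visit precede tool exposure under that pulmonologist in every group, so they mainly add common background, and the expected effect is a weaker contrast.

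**Conclusion.** The point holds in a narrow form. If item 4 is asked at the 3-month call, as the text implies, half of its recall window precedes the index visit. In reset patients that half can include comparison-arm time. The month-3 arm contrast for quit methods is then diluted, keeping 95% to 60% of its size for base rates of 5% to 40%. Those rates, the equal pre-visit rate in both arms and the independence of the two periods are assumptions; the article supplies none of them.

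Two stronger readings are not supported. Half of the window is not half of the effect: in the table the loss runs from 5% to 40%. Nor is the smoking outcome as a whole diluted: three of its four items are unaffected, and the month-6 answer to the fourth is sound. The article also names no time point or item as the analysed smoking endpoint.

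This is a minor measurement flaw in one item of a secondary outcome. The Discussion says the trial is powered for the primary outcome, which this does not touch. It is still worth settling before the calls are made, because the undated answers cannot be fully repaired afterwards.

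**What to change.** Keep the six-month wording at baseline and at the 6-month call. At the 3-month call, choose one of two options:

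- ask about methods tried *since your clinic visit on [date]*, with the date restarted at the reset visit for patients whose follow-up is reset; or
- do not ask item 4 at month 3, and state that.

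Use the 6-month answer to define any method tried since the index visit. It covers months 0 to 6 directly, including for patients who missed the 3-month call. Anchoring the month-6 question to the previous call is unnecessary and would lose months 0 to 3 for those patients.

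The cost is a wording change to one item on one form, with the visit date available to the caller. The small downside is that the month-3 wording would differ from baseline, so those two answers would not be directly comparable. Under the second option, the month-3 reading of this item is given up.

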#### Study procedures

##### Recruitment, enrollment, and consent

At the beginning of the study (where all pulmonologists are assigned to the comparison arm), the project manager will review key information from the study protocol with participating pulmonologists. All pulmonologists will be emailed the latest CTS guidelines [6] and will be provided refresher training on the guidelines, if requested. Participation in these orientation interactions, however, will not be mandatory, and lack of participation by a pulmonologist will not exclude them from the study. In addition, before switching a given pulmonologist to the intervention arm, we will provide one-on-one training sessions on the use of the ADI and patient tool. For the ADI training, emphasis will be on how the software operates and how the ADI should be used and interpreted during clinical practice. For the patient tool, the training will include a detailed walk-through of the material, and pulmonologists will have the opportunity to customize the tool according to their practice preference, in a manner that does not affect the validity and consistency of the intervention (e.g., on which monitors they want to see the notifications, how large the fonts should be). A run-in period of 1 month is considered during which training and troubleshooting will take place (Fig. 2). Data gathered during this period will not contribute to the analysis.

Data collected for the purpose of primary endpoint assessment will occur anonymously with a waiver of prior subject consent (Fig. 4). The alignment of prescribed medication with guidelines is directly targeted at measuring the relevant process-of-care variable. The information required to ascertain this endpoint is available through EHR and will be collected as aggregate data for analysis without recording any patient identifiers or changing any aspect of the COPD care being received by the individuals to whom the information relates.

**Fig. 4 Fig4:**
[figure not shown]
Participant flow chart. BMQ, Beliefs about Medicines Questionnaire; CAT, COPD Assessment Test; COPD, chronic obstructive pulmonary disease; CTS, Canadian Thoracic Society; EQ5D, EuroQoL 5-dimension

Assessment of the secondary outcomes will involve recruitment of participants into a longitudinal component and linkage with administrative health data. An informed consent process will be applied here, with subjects simultaneously being given the option to opt out of the component of the study that involves accessing and linking their data to administrative health records. Patients who are eligible for the study will be shortlisted prior to their appointment based on their charts or referral notes by the research coordinator. At the end of each eligible appointment, the site coordinators will approach patients directly to invite them to participate in the longitudinal component of the study.

##### Data collection

The total duration of the trial is 30 months. Initially, all participating pulmonologists will be in the comparison arm. After 6 months, two randomly selected pulmonologists will be reassigned to the intervention arm every other month (Fig. 2). In month 18, the last two pulmonologists will be assigned to the intervention arm, and patient recruitment will continue until month 24. Follow-up data will be collected until month 30 to ensure 6 months of follow-up data for all patients.

To assess the primary endpoint, the prescribed versus recommended treatments will be automatically documented and collected in aggregate form under a unique identification (ID) code assigned to each pulmonologist. If a patient consents to the longitudinal component, a baseline study visit will be conducted that includes administration of questionnaires to collect clinical and patient-reported data to assess secondary outcomes (Fig. 4). Subsequently, two follow-up appointments will be arranged at 3- and 6-month post initial visit via telephone. If a patient sees an enrolled pulmonologist multiple times throughout the 24-month study period, the first visit with the pulmonologist will be used to mark the start of the follow-up period for longitudinal data collection, unless the pulmonologist was reassigned to the intervention arm between visits. In this case, if the patient has consented to the longitudinal component, the follow-up period will be reset during the first visit the pulmonologist is in the intervention arm, and the patient will be followed for another 6 months after the initial intervention arm visit.

To deliver the intervention package, site coordinators will set up automatic software triggers for all eligible patients seeing a pulmonologist allocated to the intervention arm. A trigger will launch when the pulmonologist opens a patient’s EHR chart during the patient encounter, and the ADI will be pre-populated with predictor values. If a predictor value is not retrieved from a patient’s EHR, the empty fields will be highlighted and will be fillable through dictation or by typing directly into the ADI computer interface. At the end of the encounter, the pulmonologist will print the customized patient tool that will be distributed by the research coordinator.

Regarding linkage with administrative health data, clinical data required for the assessment of secondary endpoints, including hospital visits, physician visits, medication prescriptions, and medication dispensing, will be requested in datasets from BC’s Ministry of Health. These data will be requested for 1 year before and 1 year after the baseline visit for each participant and will be used to assess medication adherence and frequency of exacerbations 12 months before and after study enrollment. These data will be received as anonymized and will be hosted by Population Data BC [40], who will provide remote access for data analysis and reporting.

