**Methods:**

IMPACT will be conducted in two phases. Phase 1 will include the systematic and user-centered development of two decision support tools: (1) a decision tool for pulmonologists called the ACCEPT decision intervention (ADI), which combines risk prediction from the previously developed Acute COPD Exacerbation Prediction Tool with treatment algorithms recommended by the Canadian Thoracic Society’s COPD pharmacotherapy guidelines, and (2) an information pamphlet for COPD patients (patient tool), tailored to their prescribed medication, clinical needs, and lung function. In phase 2, we will conduct a stepped-wedge cluster randomized controlled trial in two outpatient respiratory clinics to evaluate the impact of the decision support tools on quality of care and patient outcomes. Clusters will be practicing pulmonologists (*n* ≥ 24), who will progressively switch to the intervention over 18 months. At the end of the study, a qualitative process evaluation will be carried out to determine the barriers and enablers of uptake of the tools.

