### Phase 2: A stepped-wedge cluster randomized control trial

#### Study design and setting

To test the effect of the intervention package (ADI and patient tool), we will conduct a prospective stepped-wedge cluster RCT. The unit of randomization will be staff pulmonologists at the two study sites. A stepped-wedge trial design was chosen for multiple reasons. First, clinical prediction model implementation studies should not randomize patients because of potential learning effects (changes in physician behavior after exposure to prediction model, even towards patients in the other group) [28]. Second, the stepped-wedge RCT is an implementation-oriented study design, since by the end of the trial all clusters will be assigned to the intervention arm.

In this trial, pulmonologists (clusters) will be assigned to treatment as usual (comparison arm) at the beginning of the study, with successive assignment to the intervention arm completed in a one-directional, staggered format. The one-way crossover from comparison to intervention will be allocated using a computerized random number generator and completed by the project manager during the first month of the study. Furthermore, due to the nature of the intervention, masking is not possible; thus, blinding will not be applied at the patient or cluster level. However, the allocation sequence will be concealed. Key study design features are shown in Fig. 2.

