#### Study population

Since the intervention will be embedded into the EHR as a standard clinical decision support system and will be part of routine care, all staff pulmonologists at the two study sites (*n* = 28) will participate automatically in the study. However, conservatively anticipating data from the practice of four physicians will not be used for this study for various reasons, such as an extended leave; we aim to use data from 24 pulmonologists, who will comprise the study clusters. Individual patients who are referred to one of the participating pulmonologists at a study site with a physician-assigned diagnosis of COPD will be invited to participate in the clinical trial. For inclusion, individuals must be as follows: (1) a legal Canadian resident, (2) aged 18 years and older, and (3) able to understand English.

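### The stated crossover pace, switching window and number of clusters contradict each other: two pulmonologists every other month up to month 18 moves at most 14, not 24

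*Protocol article*

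**What the plan says.** Four places in the protocol article describe the crossover.

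- **Data collection (Phase 2, Study procedures)** gives the pace: "After 6 months, two randomly selected pulmonologists will be reassigned to the intervention arm every other month". It then gives the end points: "In month 18, the last two pulmonologists will be assigned to the intervention arm, and patient recruitment will continue until month 24". It also states "The total duration of the trial is 30 months".
- **Study population (Phase 2)** counts 28 staff pulmonologists who take part automatically, allows for four whose data may not be usable, and concludes: "we aim to use data from 24 pulmonologists, who will comprise the study clusters".
- **Study design and setting (Phase 2)** gives as a reason for the stepped wedge that "by the end of the trial all clusters will be assigned to the intervention arm". It adds that the crossover is allocated by a random number generator in the first month of the study.
- **Abstract, Methods** describes at least 24 pulmonologists "who will progressively switch to the intervention over 18 months".

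The Sample size calculations section makes the design effect (2.15, then 2.18 after allowing for unequal cluster sizes) depend on the crossover pattern, the number of clusters and the run-in. The Statistical analyses section analyses each cluster by its randomised crossover time and includes time as a fixed effect over the steps.

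**The concern.** In a stepped wedge the list of switch dates is the randomisation. It fixes how many steps there are, which visits count as comparison or intervention, and how far the treatment effect can be separated from the time trend. Here the printed pace and window produce too few switch dates for the number of clusters. A statistician preparing the allocation list from this text would run out of dates with ten or more pulmonologists still unplaced. For those clusters the planned analysis by randomised crossover time has no defined input. A reader also cannot tell which schedule lies behind the design effect, and therefore behind the total of 1153.

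**Working it through.** **Inputs.** Two pulmonologists per switch date, one date every two months, starting after month 6, last switch in month 18, recruitment to month 24, trial end in month 30 (all from Data collection). 24 study clusters, 28 participating (Study population).

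**Step 1: reproduce the plan's own count of 24.** Clusters moved = 2 × number of switch dates up to month 18.

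| First switch | Dates | Moved | Unplaced of 24 | Unplaced of 28 |
|---|---|---|---|---|
| Month 6 | 6, 8, 10, 12, 14, 16, 18 (7) | 14 | 10 | 14 |
| Month 7 | 7, 9, 11, 13, 15, 17 (6) | 12 | 12 | 16 |
| Month 8 | 8, 10, 12, 14, 16, 18 (6) | 12 | 12 | 16 |

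The figure of 24 is not reproduced under any start month. The most favourable reading leaves 10/24 = 42% without a date, or 14/28 = 50% if all participants are to be scheduled.

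**Step 2: keep the pace and let the window run on.** Last switch = start + 2 × (clusters/2 − 1).

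- 24 clusters: 6 + 2 × 11 = month 28 (month 30 if starting in month 8). Recruitment has closed in month 24.
- 28 clusters: 6 + 2 × 13 = month 32 (month 34 if starting in month 8). The trial has ended in month 30.

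**Step 3: keep the window and the full count, and solve for the pace.**

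- Two per month in months 7 to 18: 12 × 2 = 24.
- Four every other month in months 8 to 18: 6 × 4 = 24.
- Four every other month in months 6 to 18: 7 × 4 = 28.

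**Step 4: the abstract.** Months 6 to 18 span 18 − 6 = 12 months of switching, against 18 in the abstract. The two agree only if the abstract counts from study start to the last switch.

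**Step 5: can the design effect reveal the intended schedule?** Use the stated intra-cluster coefficient ρ = 0.026 and cluster autocorrelation π = 0.491. *Assume* 24 equal clusters, one period before the first step and one per step, no run-in, and a total N of 1056 to 1153. With L steps, m = N/(24(L + 1)) and r = mρπ/(1 + (m − 1)ρ), a standard formula is

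DE = (L + 1)(1 + (m − 1)ρ) × 3L(1 − r)(1 + Lr) / ((L² − 1)(2 + Lr)).

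It gives about 2.24–2.27 for 6 steps, 2.16–2.20 for 7 and 1.99–2.02 for 12.

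Under a different assumption (24 monthly periods with a fixed effect for each month, and each cluster's switch month dropped as run-in), the same 12-step schedule over months 7 to 18 gives about 3.95–3.98.

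So one schedule can yield anything from about 2.0 to 4.0, depending on how the opening and closing months are treated. The printed 2.15 cannot identify the schedule. The exercise does show that the design effect depends on the schedule and on how its periods are defined.

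**The case against.** The strongest reply is that this is a slip of wording in an otherwise clear design. The design section says every cluster crosses over, and Data collection itself calls the month-18 pair the last two. Replacing the two-monthly interval by a monthly one gives exactly 24 and fits every other statement about the start, the pair size and the last switch. Fig. 2, which Data collection cites for the schedule, is not shown, nor is the supplement with the sample size details, and either may hold the correct version.

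Much of this stands. A reader might infer that ten or more clusters will never cross over, so that the trial becomes a hybrid with a permanent comparison group. The documents do not support that: they state the opposite intention, and the shortfall follows only from taking the printed pace and window literally. A reader might also infer that the design effect is wrong or the trial underpowered. That is not shown either, because the schedule used in the calculation is not visible. Nor is the abstract's 18 months a clear error, since it can be counted from study start. The figures based on 28 are secondary, because the article names 24 as the study clusters.

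What does not stand is that the unseen figure settles the matter. No figure can make two per date, every second month, up to month 18 add up to 24. If Fig. 2 is right, the Data collection text is wrong. And the article does not leave the schedule to the full protocol: it states one explicitly.

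**Conclusion.** The contradiction is real and rests on a simple count. On the most favourable reading the printed schedule gives a date to 14 of 24 study clusters and leaves 10 (42%) without one; a first switch in month 7 or 8 leaves 12. Holding the pace instead pushes the 24th switch to month 28 or later, past the end of recruitment. The only assumption is the month of the first switch, and every plausible choice was tried.

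The conclusion is limited to an inconsistency between pace, window and cluster count. The slip may well lie in the two-monthly interval, but the documents do not settle this. It still has to be corrected before the first switch, because the allocation list, the time steps in the model and the design effect all depend on the answer.

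**What to change.** State one feasible schedule that gives every randomised pulmonologist a switch date, and say whether 24 or all 28 are scheduled. Two options that fit the window:

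- **Two per month over months 7 to 18.** This places exactly 24, keeps the six-month comparison period and keeps a final pair in month 18. Only the interval changes in the text.
- **Four every other month over months 6 to 18.** This places all 28, but the number per date and the description of the final pair must be reworded.

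Starting earlier in order to keep two every other month is not a good repair. Twelve dates from month 2 end in month 2 + 2 × 11 = 24, when recruitment closes. The last pair would contribute essentially no intervention visits, and the six-month comparison period would be lost.

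Use the chosen schedule in the abstract (saying from when the 18 months are counted), the Study population and Data collection sections, Fig. 2 and the allocation list. Confirm that the design effect of 2.15/2.18 and the total of 1153 were computed on it, with the one-month run-in and the period definition stated. If they were not, restate them.

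The cost is protocol wording, a check of the figure and the allocation list, and one rerun of the sample size calculation. No extra patients are needed if the design effect is confirmed. If it is not, the required number may change.
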